### Data management and statistical analysis

Each participant will be given a unique study identification number. Data will be collected using paper-based case report forms (CRFs) and will be double entered and managed by well-trained data entry personnel using the REDCap electronic data capture tools hosted at the Leiden University Medical Center, the Netherlands, via Emory University, Atlanta, GA, USA [40].

All analyses will be conducted blinded to the treatment allocations and will be performed using STATA version 12 (StataCorp; College Station, TX, USA) or IBM Statistical Package for Social Sciences version 23 (SPSS Inc., Chicago, Illinois, USA) or R language (R Foundation for Statistical Computing; Vienna, Austria). Response and dropout rates will be assessed and reported. Demographics and outcome parameters will be summarised using descriptive summary measures, expressed as mean (standard deviation) or median (interquartile range) for continuous variables depending on whether the data are normally distributed and frequencies (percentage) for categorical variables. The proportion of participants positive for intestinal schistosomiasis will be calculated as the proportion of participants who tested positive at various time points (e.g. baseline, week 1, week 2, etc.). These percentages positive for schistosomiasis will be reported separately for each diagnostic test. Baseline characteristics between the control and intervention groups will be compared using the X^2^ test for categorical variables and *t*-test or Mann-Whitney U for continuous variables depending on the distribution of the data.

For the primary and secondary outcomes, a repeated measurements analysis approach will be used [41]. With this approach, the correlation between the measurements collected from the same participant over time will be modelled using properly chosen correlation matrices. Based on this analysis the proportions cured at different time points will be estimated and differences between the intense and standard treatment group will be tested for statistical significance. Similarly, for the IRR the progression of the reduction in intensity will be estimated and differences between the two groups at different time points will be tested for statistical significance. This model-based approach is becoming a more popular method to properly analyse longitudinal data on treatment efficacy of PZQ among individuals as well as among groups of individuals [42–44]. Transformation of data will be applied if needed. The model will be adjusted for covariates such as age and sex. Although the assumption will be made that missing data will be missing at random, reasons for individuals missing treatment at each time-point will be recorded.

In the absence of a true ‘gold’ standard, the sensitivity and specificity for KK, POC-CCA, UCP-LF CAA and PCR will be estimated by using an imperfect ‘gold’ standard (based on assumptions of 100% specificity for KK, CAA and PCR, similarly to Knopp et al., 2015 [45]) as well as by using latent class analysis (LCA). LCA uses all available data to estimate the proportion of true positives that test positive for each test (i.e. the sensitivity of each test), the proportion of true negatives that test negative for each test (i.e. the specificity of each test), and the proportion of individuals truly positive in the study population (i.e. the infection prevalence within the study population), as described previously [46, 47]. The sensitivity, specificity, positive predictive value (PPV) and negative predictive value (NPV) of all diagnostic tests will be calculated with 95% confidence intervals (CIs). For all analysis, a *p* value of < 0.05 will be taken as the level for statistical significance.

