### Outcome measures

The CR is defined as the proportion of participants who were *S. mansoni* egg positive at baseline and who became *S. mansoni* egg negative at week 8, as determined by KK. For the primary outcome, the CR in the standard treatment group will be compared to the CR in the intense treatment group. For the other diagnostic tests, the CR will be the proportion of participants who were positive by urine POC-CCA, urine UCP-LF CAA or stool PCR at baseline and who became negative at week 8. Differences between the standard and intense treatment group will be compared. The overall IRR in the intense and standard treatment groups will be calculated as the intensity of infection at week 8 compared to the intensity of infection at baseline, as determined by the different diagnostic tests (intensity referring to egg counts for KK, artificial score for POC-CCA, CAA level in pg/ml for UCP-LF CAA, Ct-value for real-time PCR). Additionally, the CR and IRR will be determined at intermediate time points after one versus two and one versus three standard doses of PZQ.

All adverse events occurring within 24 h after PZQ treatment will be recorded to evaluate the safety and tolerability of repeated PZQ treatment.

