### Sample size calculation

The sample size estimation is based on the difference in CR of one versus four repeated standard doses of PZQ measured with KK 8 weeks after treatment. Based on previous, data we assume a CR of 66% after one standard dose of PZQ [11] and aim for an increased CR of 98.7% after four repeated doses of PZQ, leading to a sample size of 30 participants per group, with a power of 90% and a level of significance of 5% (2-tail) [39]. Because we anticipate a considerable loss to follow-up, we aim to include approximately 100 participants in each group, hence 200 participants in total.

Assuming a *S. mansoni* prevalence of approximately 25% by KK (unpublished data, Taabo HDSS survey February 2016) it is estimated that at least 1000 children will have to be screened to obtain a minimum of 200 KK positives in the selected region.

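### If the correlation-matrix model for cure is an unweighted GEE, as its wording suggests, it is not in general valid under the missing-at-random assumption stated beside it

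*Protocol article*

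**What the plan says.** All statements are in the protocol article.

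- **Outcome measures** makes the primary outcome yes/no for each child: "The CR is defined as the proportion of participants who were" egg-positive at baseline and egg-negative by Kato-Katz (KK) at week 8. The arms are compared on this cure rate (CR).
- **Data management and statistical analysis** states that for primary and secondary outcomes "a repeated measurements analysis approach will be used". Correlation within a child "will be modelled using properly chosen correlation matrices", and from this "the proportions cured at different time points will be estimated" and compared between arms. On covariates: "The model will be adjusted for covariates such as age and sex".
- The same section states that "the assumption will be made that missing data will be missing at random". Besides this it says only that reasons for missed treatment will be recorded.
- **Sample size calculation** says: "Because we anticipate a considerable loss to follow-up, we aim to include approximately 100 participants in each group". The requirement is 30 per group, and no loss rate is given.
- **Ethical considerations** commits the main publication to this analysis section.

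**The concern.** Choosing a correlation matrix and estimating population proportions cured is how one usually describes a marginal GEE for a binary outcome. A GEE without weights or imputation is consistent when loss is completely random or depends only on what is in the model, such as arm, visit, age and sex. MAR is weaker. It also allows loss to depend on earlier observed results, and the stool samples taken every two weeks supply such results.

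If children who have already tested negative, or those still positive, stop bringing stool at a different rate, the children seen at week 8 are no longer representative of their arm. By the plan's own figures the arms differ widely in how many are cured, so the distortion need not cancel in the difference. What is at stake is the size of the primary cure-rate difference and the coverage of its interval. Its direction is not in doubt.

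**Working it through.** **The plan's own figure.** Inputs are 66% ("we assume a CR of 66% after one standard dose of PZQ"), 98.7%, 90% power and two-sided 5%. The mean rate is (0.66 + 0.987)/2 = 0.8235 and the difference is 0.327. The pooled-variance formula gives n = (1.960 + 1.282)² × 2 × 0.8235 × 0.1765 / 0.327² = 28.6, so 29 per group. Fisher's exact test first reaches 90% power at 29 (90.9%). The stated 30 is reproduced, and no printed number is wrong on this point. Enrolling 100 where 30 are needed leaves room for at most 70% loss. That is a ceiling, not a forecast.

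**Mechanism.** Let h be a child's KK history to week 6, r(h) the probability of being seen at week 8, and π(h) the probability of being cured at week 8. The true cure rate is Σ P(h)π(h). Among children seen it is Σ P(h)r(h)π(h) / Σ P(h)r(h). The two agree if r(h) does not vary with h. Under MAR it may vary. A modelled correlation borrows from earlier visits and so removes part of the gap, but not in general all of it.

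**Assumptions, none of them in the protocol.** Interim cure rates at weeks 2, 4, 6 and 8 are 60/64/66/66% (standard) and 60/85/95/98.7% (intense). Binary results come from a latent Gaussian with AR correlation 0.8 or exchangeable correlation 0.6. Every child gives the week 2 stool, and dropout in each later two-week interval depends only on the previous KK result. The GEE has a free mean for each arm and visit and one estimated working correlation. The table gives its large-sample bias in the week-8 difference, in percentage points. Ranges run over the two latent correlations.

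| Dropout per interval | Loss by week 8, standard / intense | Exchangeable | AR(1) | Unstructured | Independence |
|---|---|---|---|---|---|
| 33% for all | 70% / 70% | 0 | 0 | 0 | 0 |
| By arm only, 20% v 40% | 49% / 78% | 0 | 0 | 0 | 0 |
| 40% after negative, 15% after positive | 65-66% / 72% | -0.1 to +1.2 | +3.2 to +5.1 | -0.6 to +0.3 | +9.3 to +10.4 |
| 20% after negative, 45% after positive | 63% / 57% | -2.8 to -2.1 | -5.7 to -4.5 | -4.5 to -4.1 | -9.1 to -8.3 |
| Standard arm as the row above; intense arm 33% after negative, 15% after positive | 63% / 65% | -1.3 to +0.1 | -5.6 to -3.8 | -1.9 to -1.8 | -10.4 to -9.4 |
| 10% after negative, 3% after positive | 21% / 24% | +0.2 to +0.4 | +0.8 to +1.2 | +0.6 | +1.9 to +2.2 |
| 4% after negative, 12% after positive | 19% / 16% | -0.6 to -0.4 | -1.4 to -1.0 | -0.8 | -2.4 to -2.2 |

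One cell in full: with exchangeable data, positives leaving more and AR(1) working correlation, the fitted cure rates are 71.9% and 98.9%. The difference is 27.0, and 27.0 - 32.7 = -5.7.

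**Range over loss rates.** A second large-sample calculation with modelled correlation (exchangeable, AR(1) or unstructured) covered loss from 13% to 71%. The absolute bias was 0.4-1.3 points at 13-24% loss, 0.5-3.1 at 22-43% and 0.3-7.0 at 40-71%.

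**Methods that are valid under MAR.** Weighting by the inverse of the true probability of remaining returned 66.0% and 98.7% in every scenario of the table. A saturated likelihood estimate (6,000 simulated children per arm) gave differences of 32.5 to 34.6 in the heavy-loss MAR scenarios, equal to 32.7 within simulation error.

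**The case against.** The estimator is never named. The section calls its approach model-based and defers to a cited reference. The sentence on correlation matrices covers continuous intensity outcomes as well as cure. A likelihood model can also be defined through a correlation matrix (a latent-Gaussian probit with exchangeable correlation is one), and if correctly specified it is valid under exactly the assumption stated. All of this stands, so the point has to be conditional.

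Two stronger readings are tempting, and the protocol supports neither.

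- A reader might infer that the primary model is invalid as written. That would require the document to name an unweighted GEE, and it does not.
- A reader might infer a bias of 5 to 12 points with poor interval coverage. Simulation under working independence does give differences of 37.8, 45.1 or 22.4 points in place of 32.7, with coverage down to 81% or 55%. But independence is the one choice that leaves correlation unmodelled, and the plan says it will be modelled. The larger of these figures also need losses near the 70% ceiling, whereas the protocol gives no rate.

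The dropout mechanism is likewise assumed. Nothing says that children learn their interim results or that results affect attendance. A condensed article may also leave weights and imputation models to a fuller document, so their absence is not the point here. The point is that the method, on its most natural reading, and the missing-data assumption do not fit together. The main publication is to follow this section.

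**Conclusion.** The point holds in conditional form. The wording suggests a marginal GEE. If it is unweighted, the stated MAR assumption does not in general protect the week-8 cure-rate difference once dropout depends on earlier results.

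With the correlation modelled, the bias in the 32.7-point difference is about a point at the lower losses considered and up to about 7 points at the heaviest, in either direction. It depends on the working correlation, which is left open. It is nil when loss is completely random or depends only on arm. The sizes rest on assumed interim cure rates, within-child correlation and dropout rates. Even the largest would distort the estimate without reversing the conclusion. The change is worth making because it is cheap and uses data already collected. The issue does not undermine the trial.

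**What to change.** Name the estimator and make the primary week-8 analysis valid under MAR, by one of these routes:

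1. Multiply impute week-8 KK within arm.
2. Weight the GEE by the inverse probability of remaining in follow-up.
3. Fit a likelihood-based model and derive marginal cure rates from it.

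For the first two, use the earlier KK, POC-CCA, CAA and PCR results. Urine is collected weekly, so antigen results may exist where a stool is missing. Few positives are expected in the intense arm, so keep the imputation model small.

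Report the week-8 risk difference with its interval, and add one sensitivity analysis that counts missing week-8 results as not cured.

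The cost is a change of wording and modest programming, with no new data or participants. The interval may be slightly wider.

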Observed cure rates (CRs) after a single dose of PZQ treatment (40 mg/kg) range between 42 and 79% for *Schistosoma mansoni* and between 37 and 93% for *S.haematobium* in school-aged children [11]. A second dose of PZQ at a later time point can increase the CR up to 93% for *S.mansoni* [11–13] and up to 99% for *S. haematobium* [11]. However, the estimated efficacy of PZQ is highly dependent on the diagnostic tool used to measure CRs. Most studies have used traditional parasitological methods, such as the Kato-Katz (KK) and urine-filtration (UF) methods based on microscopy and determining the presence/excretion of eggs. These methods lack sensitivity for diagnosing low level infections and as such overestimate CRs [14, 15]. More sensitive diagnostic tools for schistosomiasis which are currently available and can be implemented in the field, are much more suited to evaluate the efficacy of PZQ and alternative dose regimens. For example, the commercially available point-of-care circulating cathodic antigen (POC-CCA) test, which indicates active worm infection by detection of parasite CCA in urine, has shown a high diagnostic accuracy for *S.mansoni* with a sensitivity ranging between 78 and 92% and specificity approaching 100% [15–17]. Over the past 10 years, this test has been widely evaluated in sub-Saharan Africa and is now recommended as the first line diagnostic to map schistosome prevalence and facilitate preventive chemotherapy strategic decision-making [7, 16, 18]. In addition, there is a pressing need for ultra-sensitive diagnostic tools for areas where prevalence and infection intensity have been reduced to very low levels. Such diagnostic tools are needed to confirm interruption of transmission and possibly elimination of schistosomiasis. The circulating anodic antigen (CAA) detection assay fulfills these requirements. This assay measures parasite antigen both in urine and serum using an ultrasensitive reporter technology (up-converting phosphor particles, UCP) in combination with common immunochromatography, lateral flow (LF). This UCP-LF CAA assay has shown high sensitivity and specificity for all four main schistosome species (*S.haematobium*, *S.japonicum*, *S.mansoni* and *S.mekongi*) [19–22]. In addition to the UCP-LF CAA assay, highly specific and sensitive molecular polymerase chain reaction (PCR) techniques that detect parasite-specific DNA in stool and urine have also become available [16]. The combination of worm-derived antigens and egg-derived nucleic acids, are envisaged to further increase the sensitivity and specificity of the diagnostic toolbox and allow for a comprehensive assessment of PZQ efficacy, with respect to both parasite worm dynamics and fecundity.

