### Procedures

#### Screening and informed consent

Individuals will be assessed for eligibility during a 2-week baseline screening. This will include public meetings of awareness and health education, to allow all members of the communities to be well informed on the project. During these meetings, particular emphasis will be placed on modes of transmission, associated pathologies and risk factors related to schistosomiasis in particular and intestinal worms in general. After explaining the purpose of the study in the local language, potential participants will be asked to participate. After obtaining oral and written assent from the children and signed informed consent from their parents/legal guardians, standard demographic and other characteristics (e.g. age and sex) will be collected. Participants will be asked to provide a urine sample which will be tested on site immediately for *Schistosoma* infection by the POC-CCA urine test as well as with UF. The initial screening by POC-CCA will increase the likelihood of finding participants with a positive KK. Those with a positive POC-CCA test result (scoring 1+ or higher) as well as a negative UF result, will be asked to provide one stool sample which will be examined for *S.mansoni* eggs by triplicate KK. If at least one out of three smears is positive, the participant will be asked to undergo a biological, clinical and physical examination to determine whether he/she is in good health. For the biological exam, a blood sample will be obtained and tested for haematological indicators, liver function and renal function parameters. A study physician will perform the physical and clinical examinations, which will consist of checking the participant’s physical condition as well as determining if the participant has any chronic disease(s). All participants who meet the inclusion criteria will be enrolled and randomised.

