#### Diagnostics

As part of the inclusion-exclusion process, several tests will be executed to determine eligibility for the study. Absence of pregnancy, if appropriate, will be confirmed with locally available pregnancy (HCG) tests. Infection with *S. haematobium*, will be determined by filtration of 10 mL of urine and microscopically examination, as described previously [33]. Finally, to verify a potential participant’s good health, a blood sample will be tested for basic biochemical and haematological parameters (e.g. urea, creatinine, liver enzymes and haemoglobin) in a qualified local laboratory.

All urine samples will be tested at the CSRS-Fairmed laboratory in Taabo using the POC-CCA assay (batch no.: 170522062, Rapid Medical Diagnostics, Pretoria, South Africa) as previously described [7, 17, 34]. At 20 min, valid tests will be scored as negative or positive according to a set of 10 novel artificial cassettes with inkjet-printed test lines representing negative and positive results depending on the intensity of the test line (artificial score 1–10). These novel artificial scores will be transformed into stratified positive scores of trace, 1+, 2+ or 3+. All tests will be read independently by two trained laboratory technicians. In case of discordant results, a third independent investigator will be consulted and results will be discussed until agreement is reached within 25 min. UF will be performed on urine samples collected at the final time point (week 8). Additionally, all urine samples will be examined at the LUMC using the UCP-LF CAA assay: a maximum of 2 mL urine will be analysed with a cut-off threshold of 0.1 pg/ml, as previously described [19, 35]. CAA results will be reported quantitatively in pg/ml.

From each stool sample triplicate KK thick smears will be prepared at the laboratory of CSRS-Fairmed in Taabo, using 41.7 mg templates, following standard protocols [36]. Briefly, three KK thick smears (A, B and C) will be prepared on microscope slides and examined quantitatively under a microscope by two independent, experienced laboratory technicians one (A), two (B) and three (C) days after preparation. Results will be reported as eggs per slide and converted to eggs per gram of faeces (EPG).

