### Randomisation and blinding

All participants will be randomised at baseline in a 1:1 ratio, by an independent statistician. Local nurses and physicians will not be blinded to treatment. Study personnel, laboratory technicians and investigators will be blinded. Data analysis will be performed blinded to the intervention.

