### Ethical considerations

The study is registered at ClinicalTrials.gov (reference number NCT02868385) as well as at the EU Clinical Trials Register (EudraCT, reference number 2016–003017-10) and will be conducted in accordance with the latest version of the Helsinki Declaration. The study has been approved by the National Ethics Committee of the Ministry of Health in Côte d’Ivoire (CNESVS, registration number 091–18/MSHP/CNESVS-km, 27 June 2018) as well as by the Direction de la Pharmacie, du Médicament et des Laboratoires de Côte d’Ivoire (DPML, registration number 99433-/MSHP/DGS/DPML/DAR and clinical trial number ECCI00618, 22 October 2018) and has been reviewed by the Ethics Committee of the Leiden University Medical Center in the Netherlands without any objections (CME, registration number P16.254, 11 January 2017). This study protocol, including the statistical analysis section, has been written before start of the trial. The data analysis of the main publication will follow this plan. The SPIRIT protocol checklist is given in Additional file 1.

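### The efficacy model's example covariates are age and sex; baseline egg count, counted in every child before randomisation and plausibly more prognostic, is not named

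*Protocol article*

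**What the plan says.** The analysis section of the protocol article sets the model for the efficacy outcomes: "For the primary and secondary outcomes, a repeated measurements analysis approach will be used [41". Covariates get one sentence: "The model will be adjusted for covariates such as age and sex". Under Ethical considerations the article ties the main report to this text: "The data analysis of the main publication will follow this plan".

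The baseline count exists for every participant before allocation. At screening, three smears are made from one stool sample, and "If at least one out of three smears is positive, the participant will be asked to undergo a biological, clinical and physical examination". The smears are read as counts: "Results will be reported as eggs per slide and converted to eggs per gram of faeces (EPG". Under Outcome measures, the primary cure rate is the share of egg-positive children who are egg-negative by KK at week 8. On KK and similar microscopy the Background says: "These methods lack sensitivity for diagnosing low level infections and as such overestimate CRs". On allocation the article says only: "All participants will be randomised at baseline in a 1:1 ratio, by an independent statistician".

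**The concern.** Entry requires one positive smear of three, so very light and heavy infections enter together. If KK overlooks light infections, a child who starts with few eggs is more likely to be KK-negative at week 8, whether or not the worms are gone. Starting egg count is then a natural covariate for the primary outcome. The article gives no comparable reason for age or sex.

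The yes/no baseline KK result cannot do this job, because every participant is positive at entry. Only the count carries information.

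Two things are at stake. One is precision, together with protection from a chance difference in infection intensity between the arms. The other is that a count added later, under an open list, would be harder to defend as planned.

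**Working it through.** **Inputs from the protocol article (Sample size calculation).** Cure rates 66% and 98.7%; 90% power; 5% two-sided; 30 per group required; about 100 per group to be enrolled; no loss rate stated.

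**Assumptions.** The article does not say how strongly egg count predicts cure. The odds of cure are assumed to fall by 0.5 or 1.0 on the log scale per SD of log eggs per gram (EPG). A smaller effect, 66% v 85%, is also assumed, because 98.7% is a target.

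**1. The plan's own figure.** For two proportions with pooled variance under the null, mean 0.8235 and difference 0.327:

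n = [1.96·√(2·0.8235·0.1765) + 1.282·√(0.66·0.34 + 0.987·0.013)]² / 0.327² = 26.4, so 27 per group; 33 with continuity correction.

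The exact power of Fisher's test is 0.892 at 28, 0.909 at 29 and 0.923 at 30. The stated 30 is sound. It is an unadjusted calculation, and nothing below changes it.

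**2. Why the count should matter.** Three templates of 41.7 mg hold 125.1 mg, so one egg in three smears is 1000/125.1 ≈ 8 EPG. If counts are Poisson, a child who averages one egg per three smears has three negative smears with probability e⁻¹ = 0.37, with no treatment effect at all. At ten eggs per three smears (about 80 EPG) it is e⁻¹⁰ < 0.0001. This illustrates the inference; it does not estimate the slope.

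**3. Chance imbalance.** With no balancing on intensity, the difference between arms in mean log EPG has SD √(2/n): √(2/100) = 0.14 SD units, or √(2/30) = 0.26 if only 30 per arm remain.

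**4. Gain from adjustment.** There were 1000 simulated trials per row, with a logistic model for week 8, a likelihood-ratio test, and the cure-rate difference averaged over all participants. Marginal cure rates were held fixed. The variance ratio is adjusted over unadjusted.

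| Cure rates | n per arm | Slope | Variance ratio | Power without → with |
|---|---|---|---|---|
| 66% v 98.7% (stated) | 30 | 0.5 | 1.000 | 0.98 → 0.98 |
| | 30 | 1.0 | 0.950 | 0.98 → 0.98 |
| | 100 | 0.5 | 0.979 | 1.00 → 1.00 |
| | 100 | 1.0 | 0.914 | 1.00 → 1.00 |
| 66% v 85% (assumed) | 30 | 0.5 | 0.966 | 0.47 → 0.47 |
| | 30 | 1.0 | 0.872 | 0.46 → 0.51 |
| | 100 | 0.5 | 0.995 | 0.90 → 0.91 |
| | 100 | 1.0 | 0.862 | 0.90 → 0.94 |

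With slope zero the ratio was 0.999 to 1.011, so gains of about 1% are within simulation noise. The ratio 0.862 is worth 1/0.862 = 1.16, or about 16% more participants; 0.914 is worth 1/0.914 = 1.09, or about 9%.

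**5. Bias.** At 66% v 98.7% and 100 per arm, the unadjusted difference averaged 0.326 to 0.329 against a true 0.327.

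**6. Sparse failures.** At 98.7% cure, 100 × 0.013 = 1.3 failures are expected in the intense arm. The chance of none is 0.987¹⁰⁰ = 0.27, or 0.987³⁰ = 0.68 with 30 evaluable. With none, ordinary logistic regression gives no finite estimate for treatment.

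The simulation uses one time point, no missing data, and no age or sex. The planned repeated-measurements model could gain somewhat more or less.

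**The case against.** The strongest reply is that the list is open. 'Such as' introduces examples, so a reader who infers that the plan rejects baseline egg count goes beyond the text. That stands: the count is unnamed, not excluded. A journal article may also leave the full covariate list, and any balancing factors in the randomisation, to documents not shown. For that reason the brief account of allocation is not criticised here. The covariate sentence differs because the article states it and says that the main publication will follow it; examples alone do not fix the primary model.

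A reader might also infer that the cure-rate comparison is biased or invalid. It is not. Randomisation protects it, and the usual standard error already allows for chance imbalance. The article also plans analysis blinded to allocation, which softens the worry about covariates chosen after the data are seen. It does not settle which covariates enter.

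Nor does the article call baseline count the main predictor of cure. Its Background remark concerns KK sensitivity in general, and the step to baseline count is an inference. For the intensity reduction rate, baseline is already part of the outcome's definition.

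Finally, adjustment has a cost, because failures in the intense arm may be too few for an ordinary logistic fit. That stands too. The problem comes from the treatment term, however, so a logistic model with age and sex alone would meet it as well.

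**Conclusion.** The point holds as a modest improvement. The protocol article names age and sex as examples and leaves out a baseline measure that is complete before randomisation and plausibly closer to the primary outcome than either. The loss is precision and conditional balance, not validity.

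At the stated cure rates the gain is small: about 2% to 9% less variance at 100 per arm, with power already at its ceiling. It matters more if four doses do less than hoped: up to about 14% less variance at 66% v 85% with 100 per arm, and power of 0.91 to 0.94 instead of 0.90. All of this rests on the assumed slopes and, for the last figures, on the assumed 85%. No sample-size figure needs to change.

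**What to change.** Replace the covariate sentence with:

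> The primary cure-rate model will be adjusted for log baseline EPG, age and sex. Cure-rate models for the other tests will be adjusted for baseline intensity on that test's own scale (log CAA level, POC-CCA score, untransformed Ct). The effect will be reported as a standardised difference in cure rate, averaged over the covariates of all participants, using penalised (Firth-type) estimation if failures are sparse.

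The log of EPG always exists, because every participant has at least one positive smear. One log rule for all tests would not suit: the POC-CCA reading is an ordered score, and Ct is a cycle number already on a log-type scale.

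No new data are needed. The cost is slightly more analysis work and a method that copes with few or no failures in the intense arm. Plain Firth estimation pulls predicted probabilities towards one half, so the predictions should be corrected before they are averaged. A penalised fit within a repeated-measurements model also takes more setting up than a week-8 logistic fit.
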